##### Definition of evaluation analysis group

2.8.4.1.

The FA set is defined as all subjects who are randomly assigned to this clinical trial, subjected to a test device or false procedure at least once, and evaluated for effectiveness. The per-protocol (PP) set is defined as all subjects who had completed a clinical trial without protocol violation among the subjects included in the FA set. However, if dropouts or significant clinical trial plan violations do not affect the validity evaluation, they may be included as PP sets, which are discussed, determined, and documented prior to de-blinding for statistical analysis. An effectiveness analysis will be performed for each of the FA and PP sets; if the subjects, including the analysis group, are different, all results will be presented. The final validity evaluation will be based on FA results.

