##### Implementation of occupational therapy

2.4.1.1.

OT will be provided twice a day for 30 min each, starting within 10 min after rTMS in both the intervention and control groups between T0 and T1. Participants will receive one-on-one OT with an occupational therapist, comprising task-oriented therapy, including shaping exercises. The difficulty will be tailored to each participant and will be gradually increased according to the improvement in the motor function of the paralyzed hand. Therapists will be blinded to the participant groups throughout the trial. Participants will be provided with a rehabilitation diary, and the therapy dosage will be recorded during the period between T1 and T2. In the rehabilitation diary, the date and duration of rehabilitation treatment in minutes will be recorded as items of occupational therapy, physical therapy, or other treatment.

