#### Primary outcome measure

2.5.1.

Primary outcome is the amount of change in the number of Box and Block Test (BBT) (17) at T2 compared to that at T0 (3, 5, 13, 18). The BBT is a manual dexterity test that has been used to evaluate physically disabled individuals. The BBT consists of a partition and wooden box divided into two compartments containing 150 blocks. Participants will be asked to move as much as possible, one at a time, from one compartment of the box to another of the same size, within 60 s. The BBT score is the number of blocks the participant has moved (17).

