#### Secondary outcome measures

2.5.2.

Several secondary outcome measures will be assessed (Table 2), including: changes in the number of BBT at T1 compared to those at T0; UE-FMA (19) score changes at T1 and T2 compared to those at T0 (3, 13, 20); changes in the Korean version of Modified Bartherl Index (K-MBI) (21) score at T1and T2 compared to those at T0 (13, 22); changes in the NIH Stroke Scale (NIHSS) scores (23) at T1 and T2 compared to those at T0 (12, 13, 24); the finger tapping test (FTT) (25) (participants tap their index fingers as quickly as possible within a 10-s time interval, and the number of times they tap their fingers becomes an FFT score) score changes at T1and T2 compared to those at T0 (13, 24); the Brunnstrom Stage (26) changes at T1and T2 compared to those at T0 (13); the Modified Ashworth Scale (MAS) score changes at T1and T2 compared to those at T0 (13, 22, 27); and the degree of change in grip strength (hand grip, pinch grip, lateral pr, and three-jaw chuck) measured using the JAMAR dynamometer (Performance Health Supply Inc., Cedarburg, United States) at T1 and T2 compared to that at T0 (3, 13, 22).

**Table 2 tab2:** Timetable and measures to be made.

	Intervention period		4 weeks after EOT (T2)
	Baseline (T0)	EOT (T1)	

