### Sample size

2.6.

According to a previous study (13), the average change in BBT at 1 month after baseline was confirmed to be 17.40 (9.80) in subcortical and brainstem stroke subjects who underwent rTMS and 10.90 (10.30) in subjects who received sham stimulation. The average change in BBT in the intervention and control groups in this clinical trial is also expected to be similar, and the standard deviation is assumed to be a large value of 10.30 for the conservatively setting. Assuming a significance level of 5% and a power of 80% under a BBT average change of 6.50 (intervention group: 17.40, control group: 10.90) and a standard deviation of 10.30, the number of subjects calculated is at least 40 per group; therefore, a total of 88 subjects will be recruited, considering a 10% dropout rate.

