#### Analysis of primary outcome

2.8.3.

Descriptive statistics (number of participants, mean, standard deviation, median, minimum, and maximum) of the BBT values at T0 and T2 and the degree of BBT change between T0 and T2 will be presented by group. The statistical significance of BBT changes between groups will be confirmed by analysis of covariance (ANCOVA) with the number of BBTs at T0 and stratified variables (depending on whether the UE-FMA score is less than 28 points) and occupational therapy dosage between T1 and T2 as covariates. Additionally, in the subgroup analysis, the location of stroke lesions will also be included as a covariate in the ANCOVA. All statistical analysis will be performed with significance level of 0.05.

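### The primary single-visit ANCOVA makes no use of T1 BBT when T2 is missing; a T1/T2 repeated-measures model without the post-T1 therapy covariate would be a modest, low-cost improvement

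*Protocol article*

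**What the plan says.** - **Endpoint** (section 2.5.1, on the primary measure): "Primary outcome is the amount of change in the number of Box and Block Test (BBT) (17) at T2 compared to that at T0".
- **Primary test** (Analysis of primary outcome, 2.8.3): the group difference in that change "will be confirmed by analysis of covariance (ANCOVA) with the number of BBTs at T0 and stratified variables", plus "occupational therapy dosage between T1 and T2 as covariates".
- **Source of the last covariate** (Implementation of occupational therapy, 2.4.1.1): "Participants will be provided with a rehabilitation diary, and the therapy dosage will be recorded during the period between T1 and T2". Study design (2.1) adds that patients or caregivers document therapy doses at T1 and T2.
- **T1 BBT**: measured at T1 as scheduled in Table 2. It is a secondary outcome in 2.5.2 ("changes in the number of BBT at T1 compared to those at T0") with its own ANCOVA in 2.8.4, and has no part in the primary model.
- **Analysis set** (2.8.4.1): FA participants must have been randomised, "subjected to a test device or false procedure at least once, and evaluated for effectiveness". No visit is attached to the evaluation. The final conclusion rests on the FA set.
- **Dropout** (Sample size, 2.6): 88 are to be recruited, "considering a 10% dropout rate".
- **Withdrawal** (2.9): participants who withdraw are encouraged to attend the scheduled follow-up visits.

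**The concern.** The set that decides the trial and the model that decides it may not hold the same people. A participant treated and assessed at T1 but lost before T2 can meet the FA definition. An ANCOVA of T0–T2 change has no outcome for that participant unless one is imputed.

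The therapy covariate adds to this. It comes from a diary covering the interval in which the participant is lost, so it is likely to be missing or cut short for the same people.

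T1 falls at the end of the 10 treatment days and T2 four weeks later. If staying to T2 depends on recovery by T1, and treatment changes recovery by T1, completers in the two arms are no longer comparable. The T1 measurement that could correct for this is already collected. At stake are some bias in the estimated T2 effect and a little precision.

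**Working it through.** **1. The plan's own figure.** Inputs from 2.6: difference 6.5, SD 10.3, power 80%, significance level 5% (two-sided reproduces the result).

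n per arm = 2 × (1.960 + 0.842)² × 10.3² / 6.5² ≈ 39.4, rounded up to 40. Then 40 × 1.1 = 44 per arm, 88 in total. The stated figures reproduce.

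**2. What 10% loss leaves.** 44 × 0.9 = 39.6 completers per arm. Normal-approximation power is Φ(6.5/10.3 × √(39.6/2) − 1.960) = Φ(0.848) = 80.2%. With no loss it is 84.1%. The planned loss is therefore already budgeted.

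**3. Precision recovered if dropout is random and occurs after T1.** The variance of the two-visit likelihood estimate relative to the completer estimate is 1 − ρ²d, where ρ is the T1–T2 correlation of BBT change (assumed) and d = 0.10.

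| ρ | 1 − ρ²d | Effective n per arm | Power |
|---|---|---|---|
| 0.5 | 0.975 | 39.6/0.975 = 40.6 | 81.2% |
| 0.7 | 0.951 | 39.6/0.951 = 41.6 | 82.1% |
| 0.85 | 0.928 | 39.6/0.928 = 42.7 | 83.0% |

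The gain over 80.2% is about 1 to 3 points.

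**4. Bias when missing T2 depends on T1.** This was simulated with 20,000 trials per setting and 44 per arm. The T2 effect of 6.5 and SD of 10.3 come from 2.6. Not in the protocol, and therefore assumed: a T1 effect of 5, the same SD at T1, all loss after T1, about 10% dropout, and log-odds of dropout rising by 1 for each SD of poorer T1 change. The completer difference is compared with the two-visit maximum-likelihood estimate.

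| Mechanism | ρ = 0.5 | ρ = 0.7 | ρ = 0.85 | Two-visit model |
|---|---|---|---|---|
| Same in both arms | −0.19 | −0.23 | −0.31 | within 0.05 of 0 |
| T1-dependent in control arm only | −0.50 | −0.66 | −0.82 | within 0.05 of 0 |

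The first row is 0.2–0.3 block, or 3–5% of 6.5. A repeat of the second setting gave completer means of 5.6 to 6.0, so the range quoted is 0.5–0.9 block (0.5/6.5 = 8% to 0.9/6.5 = 14%).

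With no treatment effect at either visit, the same-in-both-arms mechanism gives no bias, so it only attenuates. The control-only mechanism does not depend on a treatment effect, and its sign reverses if it is the good responders who leave.

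**5. Limit of the remedy.** If control-arm dropout depends on the unseen T2 value instead, at 10% the completer bias is about −0.95. The two-visit model leaves −0.72, −0.49 and −0.30 for ρ = 0.5, 0.7 and 0.85. Bias is reduced but not removed.

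**The case against.** ANCOVA is a standard and valid primary analysis for an endpoint at one visit, and 2.8.3 contradicts nothing by choosing it. That stands: this is an improvement, not the correction of an error.

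A reader might infer from 2.8.4.1 that participants without T2 are excluded from the FA set. The text does not say so. It names no visit, and a participant seen only at T1 can qualify. A reader might also fault the article for giving no missing-data rule. Imputation is neither stated nor ruled out, and such rules commonly sit in an analysis plan that is not shown, so their absence is not the point. What remains is that the article does state the primary model, and T1 BBT is not in it.

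The dropout mechanism is assumed. The protocol gives no timing of loss and no link between leaving and T1 response, and section 2.9 tries to keep withdrawn participants in follow-up. Some of the 10% may be lost during the treatment days, before T1, where a repeated-measures model recovers nothing. All of this stands and limits the size of the claim.

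Finally, replacing the ANCOVA with a mixed model while saying nothing about the T1–T2 therapy dosage would either keep excluding the same participants or change the adjustment set unannounced. That is correct, and the fix has to address it openly.

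**Conclusion.** The point holds as a modest improvement. As written, and without imputation, T0 and T1 data from a participant who misses T2 do not enter the primary test, even though that participant may be in the FA set.

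At the planned 10% dropout and under the assumptions shown, the completer estimate is off by about 0.2–0.3 block if T1-dependent loss works alike in both arms, and by about 0.5–0.9 block if it occurs only in the control arm. The power to be gained is about 1–3 points.

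Three stronger readings are not supported:
- **That the two-visit model removes dropout bias in general.** It does so only if T2 is missing at random given T0, T1, stratum and arm, and T1 was observed.
- **That bias above 10% of the effect should be expected.** With the same mechanism in both arms it needs both more than the planned dropout and a steeper dependence on T1. At 10% it needs arm-specific dropout, for which the protocol gives no evidence.
- **That the trial is underpowered for this reason.** The 10% loss is already in the sample size.

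**What to change.** Make the primary analysis a likelihood-based repeated-measures model of BBT change at T1 and T2. Its terms are treatment × visit, T0 BBT × visit, UE-FMA stratum and institution (randomisation is stratified within institution, 2.3), with an unstructured covariance. The treatment contrast at T2 is the primary test, so the endpoint is unchanged.

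Define the set as all randomised participants with at least one real or sham procedure and at least one post-baseline BBT. This also settles which evaluation qualifies for the FA set.

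State explicitly that occupational therapy dosage between T1 and T2 is left out of this model, because it is a post-randomisation diary value likely to be missing for those who miss T2. Keep the planned ANCOVA with that covariate as a sensitivity analysis.

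The cost is a change of wording and a standard model fit, to be settled before unblinding, using data already scheduled. Reporting becomes slightly more complex. Because the covariate set changes, the result can differ somewhat from the planned ANCOVA even with complete data.

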### Participant safety and withdrawal

2.9.

A few severe adverse effects can occur during rTMS. Common side effects are mild, such as headaches and rarely reported occurrences of accidental seizures or induced hypomania (8). When a participant complains of these symptoms, the researcher will provide the necessary treatment with intensive observation. The summary and analysis of Treatment Emergent Adverse Event (TEAE) that occurs during and after the application of rTMS, descriptive statistics (number of participants, incidence, and number of occurrences) for TEAE, Adverse Device Effect (ADE), and serious adverse event (SAE) during and after the application of rTMS for clinical trials by group will be presented, and the difference in ratio between groups will be analyzed using the Chi-square test or Fisher’s exact test. The number of patients, incidence, and occurrences of coded abnormalities are presented by group using MedDRA to code abnormalities (TEEAE), medical device abnormalities (ADE), and critical abnormalities (SAE) after the application of clinical trial medical devices. The TEAE, ADE, and SAE that occurred after rTMS application were coded according to SOC and PT using MedDRA, and the number of participants, incidence, and occurrence of coded abnormal cases will be presented by group. In addition, a detailed list of individual participants who experienced significant abnormalities will be presented.

Participants are allowed to leave the trial at any time. Participants could withdraw from the trial after informing the research team; they will be encouraged to visit the prescheduled follow-ups, even if they withdraw from the study for data collection.

## Discussion

3.

This study was designed as a multi-center, double-blind, randomized sham-controlled trial that aims to confirm the efficacy of low-frequency contralesional rTMS in the recovery of upper limb motor function in patients with subcortical or brainstem ischemic stroke. To ensure the rigor of the investigation, the participants will be stratified into two subgroups based on their initial severity. Moreover, the amount of OT and PT will be the same in the intervention and control groups during the intervention period, and the amount of total therapy will be recorded throughout the trial. By controlling and recording the potential cofounders of the motor recovery after stroke, the study results are anticipated to report high-quality evidence on the effectiveness of rTMS on motor recovery after stroke.

In this study, among various rTMS protocols, low frequency rTMS over the contralesional M1 will be applied in attempts to normalize imbalance of IHI by suppressing the over-inhibition of contralesional M1 toward ipsilesional M1 (9). In previous studies, low-frequency rTMS was often chosen over high-frequency rTMS because of the low risk of seizures in the healthy corticospinal system and its minimal effect on motor behavior (8, 10). However, previous results regarding the efficacy of low-frequency rTMS over the contralesional M1 for motor recovery in patients with acute and subacute stroke remain inconsistent. Khedr et al. (24) reported that low-frequency rTMS is more advantageous in recovering upper extremity function after stroke compared to high-frequency rTMS. Dafotakis et al. (29) also reported the possible beneficial effects of low-frequency rTMS on hand function recovery in patients with acute and subacute subcortical stroke. In contrast, other studies have reported no significant beneficial effects of low-frequency rTMS compared with sham rTMS (30, 31). In a meta-analysis, Hsu et al. (11) confirmed the effect of low-frequency rTMS on the recovery of upper extremity function in patients with stroke and reiterated the notion that post-stroke hemisphere competition is altered and that this imbalance can be resolved by reducing the cortical excitability of unaffected hemispheres through low-frequency rTMS.

Recently, it has been reported that the location of stroke lesions is a key factor in the efficacy of rTMS in upper limb motor recovery. Kim et al. (13) confirmed that the recovery of the upper extremities was significant only in patients without cortical invasion. Ameli et al. demonstrated that high-frequency rTMS on the ipsilesional M1 was effective only in patients with subcortical stroke and not in patients with additional cortical stroke (32). Nowak et al. (33) conducted cross-over investigation in patients with subacute subcortical stroke and found that application of rTMS to the contralesional M1 improved the kinematics of finger and grasp movements in the affected hand. Based on these findings, the target population of this trial was narrowed down to patients with subacute subcortical or brainstem ischemic stroke. Previous studies have explained possible reasons for the better effects of rTMS in patients with stroke without cortical involvement. First, the expected increase in cortical activity in the ipsilesional M1 through rTMS is inefficient in propagating to other nodes of the motor network for motor recovery, as there is a structural or functional disconnection in stroke that invades the cortex (32, 34). Second, in the cortical brainstem, GABAergic intracortical inhibition is greater, and concurrent downregulation of GABA receptors in both hemispheres has been identified, which may be associated with the reduced effects of rTMS (13).

We also stratified the participants into two subgroups based on the initial UE-FMA score because it has been reported that rTMS can be less effective in patients with stroke with severe upper extremity paralysis. Ludemann-Podubeck et al. (35) insisted that when a larger part of the M1 or its corticospinal projections is involved in stroke, causing a more profound clinical hand motor deficit, the contralesional dorsal premotor cortex may have a positive influence on motor recovery. Therefore, low-frequency rTMS of the contralesional M1 may not help to restore functionality (35). Two other studies referred to the same mechanism and explained the correlation between the degree of paralysis and the effect of rTMS (36, 37). Based on these results, we excluded patients with stroke with extremely severe upper extremities paralysis (UE-FMA score of 15 or less and those with a wrist score of less than 1 and a hand score of less than 1) and stratified into two subgroups (UE-FMA score of 28 or higher and UE-FMA score below 28) to ensure that the initial severity in both the intervention group and control group is evenly distributed.

In this clinical trial, the change in the number of BBT at 4 weeks after EOT compared with that at baseline has been set as the primary efficacy evaluation variable. The BBT has been used in various rehabilitation studies since 1994, when its reliability and validity were verified as measures of hand function in the elderly (38); it is often used as a clinical variable to confirm hand function status and total agility of the upper limb, especially in patients with stroke (3). Accordingly, BBT has also been used as an effectiveness evaluation variable in various studies to evaluate the recovery of upper limb motor function using rTMS in patients with stroke (3, 5, 13, 18). The UE-FMA is more useful in assessing abnormalities of movement, whereas the BBT is more suitable for evaluating activity limitations (39). However, with UE-FMA, it is difficult to confirm the response to the treatment of patients with stroke with mild upper limb hemiplegia due to the ceiling effect. Therefore, in this study, the primary outcome measurement has been chosen as the change in the BBT.

This study has a few limitations. First, in the control group, a sham coil will not be used for sham rTMS. Instead, the real coil will be positioned perpendicular to the scalp with an intensity of 100% of the patient’s RMT, and the frequency and position will be the same as those in the intervention group. Although the electrical field induced by this sham stimulation method is lower and less focal than that of real stimulation (40), we cannot rule out the possibility that this low electric field strength may influence the modulation of cortical neurons. However, it has been reported that the intensity of sham stimulation is significantly weaker than that of real stimulation, suggesting a low likelihood of producing similar physiological effects as actual stimulation (41). To ensure the blindedness of the participants during intervention, the position of the coil will be placed and removed by the researcher to ensure that the participants cannot see the position of the coil throughout the intervention. Moreover, as all the participants in this study are patients with first-time stroke, there is little possibility that they could guess the group assigned to them because they may not have encountered rTMS equipment before. Second, in this study, a navigation system will not be used to determine the motor hotspots, which requires a separate MRI sequence for treatment and is difficult to apply in real clinical settings. We will use the Motor Evoked Potentials (MEP) of the First Dorsal interossei (FDI) muscle to determine motor hotspots because it has been reported that the method of finding the rTMS motor hotspot by MEP of the FDI muscle may be more effective than navigated rTMS (42).

## Conclusion

4.

This study is expected to provide evidence of the efficacy of upper limb motor function recovery using contralesional low-frequency rTMS in patients with subcortical and brainstem ischemic stroke.

## Ethics statement

The studies involving humans were approved by institutional review boards of Seoul National University Bundang Hospital and Chungnam National University Hospital. The studies were conducted in accordance with the local legislation and institutional requirements. Written informed consent for participation in this study was provided by the participants’ legal guardians/next of kin.

